# A stepped-wedge randomised controlled trial assessing the implementation, effectiveness and cost-consequences of the EDDIE+ hospital avoidance program in 12 residential aged care homes: study protocol

**DOI:** 10.1186/s12877-021-02294-8

**Published:** 2021-06-05

**Keywords:** Residential aged care facility, Nursing home, Early detection, Deterioration, Acute care, Economic evaluation, High value care, Elderly, Hospital transfer, Emergency department

## Abstract

**Background:**

Older people living in residential aged care homes experience frequent emergency transfers to hospital. These events are associated with risks of hospital acquired complications and invasive treatments or interventions. Evidence suggests that some hospital transfers may be unnecessary or avoidable. The Early Detection of Deterioration in Elderly residents (EDDIE) program is a multi-component intervention aimed at reducing unnecessary hospital admissions from residential aged care homes by empowering nursing and care staff to detect and manage early signs of resident deterioration. This study aims to implement and evaluate the program in a multi-site randomised study in Queensland, Australia.

**Methods:**

A stepped-wedge randomised controlled trial will be conducted at 12 residential aged care homes over 58 weeks. The program has four components: education and training, decision support tools, diagnostic equipment, and implementation facilitation with clinical systems support. The integrated Promoting Action on Research Implementation in Health Services (i-PARIHS) framework will be used to guide the program implementation and process evaluation. The primary outcome measure will be the number of hospital bed days used by residents, with secondary outcomes assessing emergency department transfer rates, admission rates, length of stay, family awareness and experience, staff self-efficacy and costs of both implementation and health service use. A process evaluation will assess the extent and fidelity of program implementation, mechanisms of impact and the contextual barriers and enablers.

**Discussion:**

The intervention is expected to improve outcomes by reducing unnecessary hospital transfers. Fewer hospital transfers and admissions will release resources for other patients with potentially greater needs. Residential aged care home staff might benefit from feelings of empowerment in their ability to proactively manage early signs of resident deterioration. The process evaluation will be useful for supporting wider implementation of this intervention and other similar initiatives.

**Trial registration:**

The trial is prospectively registered with the Australia New Zealand Clinical Trial Registry (ACTRN12620000507987, registered 23/04/2020).

**Supplementary Information:**

The online version contains supplementary material available at 10.1186/s12877-021-02294-8.

## Background

In Australia, residential aged care (RAC) homes provide care and accommodation for older people who can no longer be supported to live in the community. Also referred to as residential aged care facilities or nursing homes, they involve the provision of daily personal care to residents as well as clinical support from qualified nursing staff. More than 200,000 Australians currently live in RAC homes [1].

Many residents are frail and their priority for medical care is good management of escalating comorbidities [2]. Yet, residents are often transferred to hospital after experiencing an acute deterioration in health [2, 3]. Previous studies have shown that up to one third of admissions in this cohort are potentially preventable [4–6]. A recent report from the Australian Medical Association estimated that there were over 27,000 potentially preventable hospital admissions from RAC homes in 2020–21, which translated to approximately 160,000 patient bed days and $AU 312 million in hospital costs [7]. In addition to unnecessary hospital admissions, residents may be transferred to emergency departments (EDs) for relatively minor conditions and then returned to the RAC home without admission. There were an estimated 49,000 of these non-admitted ED presentations from RAC homes in 2020–21, accounting for $AU 112 million in transport and ED triage costs [7].

There are several reasons why avoiding unnecessary hospital transfers and admissions is an important goal. A systematic review of outcomes following emergency transfer to hospital for residents of RAC homes found they were associated with high rates of in-hospital complications, with up to 80% of residents experiencing potentially invasive interventions and up to 34% dying in hospital [8]. There is evidence that hospital transfers are stressful for residents and their families, who prefer care to be provided in a familiar home environment [9]. Hospital admissions are also costly, and it is important to ensure they represent a high value use of resources.

The ‘Early Detection of Deterioration In Elderly residents’ or ‘EDDIE’ program is based on a model of care originally developed and piloted at one RAC home in Queensland, Australia [10]. The program aimed to prevent unnecessary hospital admissions by enhancing the ability of RAC home staff to respond appropriately to early signs of deterioration among residents. It involved provision of training and education, decision support tools, diagnostic equipment and tailored implementation strategies.

Evaluation of this pilot study found that EDDIE was feasible and well received [11]. Nursing staff reported feeling more confident and expressed a preference for managing residents within the RAC home, while personal care workers reported better collaboration with nursing staff [11]. The program reduced hospital transfer rates and average length of stay for residents admitted to hospital, resulting in a 41% reduction in total hospital bed days. A cost-effectiveness analysis found that the program had an 86% likelihood of being cost-effective [12].

An adapted version of the pilot program, named EDDIE+, has been developed to strengthen the successful elements of the pilot program and enhance the ability for the program to be scaled up, implemented, evaluated and sustained across a number of RAC homes. This study will implement EDDIE+ in 12 RAC homes operated by the study partner Bolton Clarke, a not-for-profit aged care provider. The program will adopt implementation science methods for embedding and sustaining change. The primary aim of the study is to reduce the number of hospital bed days used by RAC residents. The program will be evaluated using a Type 1 hybrid design [13] to simultaneously assess implementation, effectiveness, and health service outcomes.

## Methods and design

### Study design

This study will adopt a stepped-wedge randomised controlled trial design (Fig. 1). Four phases will be sequentially rolled-out over 58-weeks: preparation; baseline (usual care) exposure; intervention introduction; and intervention exposure. The timing of the crossover from usual care to intervention introduction will be randomly allocated by the study statistician ([name]). Individual RAC homes will be notified of their intervention introduction date by the project team 10 weeks prior to commencement, to allow for adequate preparation time.

**Fig. 1 Fig1:**
[figure not shown]
Stepped-wedge study design in 12 RAC homes

### Setting and participants

The trial will be undertaken at 12 RAC homes in Queensland, Australia. Data will be collected from five participant groups:
RAC homes will be enrolled in the study as the main participant group. For inclusion, the RAC homes must be located in Queensland and be operated by the study partner, Bolton Clarke, a not-for-profit aged care provider. We will purposively sample from 21 eligible homes to ensure the program is implemented across a range of regional and metropolitan settings. A lower priority will be placed on homes with existing locally implemented hospital avoidance programs to minimise potential confounding with our study intervention. A lower priority will also be placed on homes with lower bed numbers to minimise the risk of underpowering the study.All nursing staff and personal care workers at each enrolled RAC home will participate in the study, with no exclusion criteria.Data on all residents at each enrolled RAC home will be collected as part of the study, with no exclusion criteria. A waiver of consent has been granted for resident data collection in recognition of the low privacy risk and negligible participant burden, as data will be de-identified and obtained indirectly from routinely collected databases and chart notes.All family members or nominated advocates of residents at each enrolled RAC home will be invited to participate in the study, with no exclusion criteria.A purposive sample of key internal and external stakeholders at each enrolled RAC home will be invited to participate in the study, with no exclusion criteria.

### Intervention

The EDDIE+ program is a multi-component intervention focused on improving quality of care. It aims to educate, engage and empower RAC home staff to identify early signs of deterioration in residents and proactively intervene to avoid unnecessary hospital transfers and admissions. An implementation science-based approach is embedded within the program to support system, process and staff behaviour change with the aim of enhancing the acceptability and sustainability of the program.

EDDIE+ comprises four core components that can be tailored to meet the needs of the local context. These are: staff education and training; decision support tools; diagnostic medical equipment; and implementation facilitation (Fig. 2). The program adopts a holistic approach that seeks to engage all nurses and personal care workers within the home. It is expected that improvements from each of the core elements working synergistically will lead to sustained change via key mechanisms of impact including staff empowerment, cultural change and systems change. An intervention logic model outlining important contextual factors and mechanisms of impact is included in Additional file 1.

**Fig. 2 Fig2:**
[figure not shown]
EDDIE+ intervention components and mechanisms of impact

### Core components

The key activities to be included within each of the four core components have been defined, with varying levels of flexibility in their implementation, as follows:

#### Education and training of all nursing staff and personal care workers

Initial face-to-face training will be provided to all nursing staff and personal care workers, with a focus on early identification of deterioration and response, including roles/responsibilities of each staff member. Training will be mandatory and will be delivered by a nurse educator employed as part of the EDDIE+ study. Separate content and training sessions will be provided to nursing staff and personal care workers to reflect the different roles and responsibilities required of these positions. The length, intensity, delivery methods and depth of content coverage of the training will be adapted to suit the needs of each site. An educational materials toolkit will be developed including core content that the nurse educator must cover for all sites, and additional materials for use as required.

#### Decision support tools

A core decision support tool covering clinical decision-making pathways for managing deterioration across a number of specific conditions (e.g., dyspnoea, chest pain, dehydration) will be developed. This will be made available in hard or electronic copy depending on the needs and preferences of the local sites. Optional use of observation charts and communication tools will be made available.

#### Diagnostic medical equipment

The study will provide equipment to each RAC home based on an initial needs assessment, to include bladder scanners, electrocardiogram machines, vital signs monitors and pulse oximeters. Appropriate use of the equipment will be covered in the training sessions and educational materials.

#### Implementation facilitation and support

Each site will identify an internal EDDIE+ facilitator. This person will be in an existing clinical leadership position in the RAC home. The EDDIE+ facilitator will dedicate up to 1 day per week for the duration of the intervention phase to the implementation, facilitation, and data monitoring activities. A facilitator guide will be developed as a resource to support dedicated EDDIE+ facilitators in their role. This will include information on the nature of project team support available throughout the project as well as a set of resources to help guide the facilitation. Examples include templates for documenting engagement activities and/or other data collection requirements. RAC home executive/management will provide ongoing support, including through leadership presence at initial training and regular ongoing communication. EDDIE+ facilitators will assist the project team with local General Practitioner (GP) practice engagement, in recognition of GPs as key decision makers in RAC home hospital transfers. EDDIE+ facilitators will assist the project team with family engagement in recognition of the important role families play in resident care decisions.

### Implementation process and framework

EDDIE+ will adopt the integrated Promoting Action on Research Implementation in Health Services (i-PARIHS) framework to guide implementation and process evaluation. i-PARIHS is a widely used implementation framework which recognises the critical role of facilitation in assessing, aligning and integrating key implementation constructs [14]. Specific constructs defined within the framework that can act as barriers or enablers of implementation include the characteristics of the innovation to be implemented, the response of intended recipients of the intervention and contextual factors (across local, organisational and external levels).

The implementation of EDDIE+ will involve an initial environmental scan of recent and current hospital avoidance programs in place within Queensland RAC homes, and subsequent identification of adoption by Bolton Clarke homes. A more detailed context mapping exercise will then be conducted for each of the 12 enrolled RAC homes to generate a baseline context assessment against the i-PARIHS framework [15]. This process will determine readiness for change and potential enablers and barriers to change, such as the level of support among RAC home management and local GPs. A tailored implementation plan will be developed for each site based on the context mapping exercise. The implementation plan will detail the fixed and flexible elements to be adopted within each of the four core components, to support and monitor intervention fidelity.

### Monitoring and evaluating implementation

Process evaluation is an essential part of designing and testing complex interventions [16]. The real-world setting and length of this trial will require a pragmatic approach to intervention adherence, reach and fidelity. The project team, with the assistance of the local EDDIE+ facilitators, will systematically monitor the implementation of the program as part of the process evaluation, using templates and approaches based on the i-PARIHS constructs. This embedded approach will aim to provide direct support for implementing the program and will inform understanding regarding how the actual implementation process contributed to the study outcomes.

To ensure the innovation maintains relevance and is responsive to the diverse RAC home staff and contexts, this implementation phase will be an iterative cycle of Plan, Do, Study, Act [17]. Intervention fidelity of the program will be monitored during the iterative evaluation process. The EDDIE+ program will be mapped to the ‘Template for Intervention Description and Replication’ (TIDieR) checklist and guide [18] to promote the replicability of this research.

### Outcomes

The study outcomes and associated outcome measures are described in Table 1. They encompass measures of program effectiveness, cost consequences and implementation process.

**Table 1 Tab1:** EDDIE + program outcome measures

Outcome label	Outcome	Outcome measures
**Effectiveness outcomes**		
Primary outcome (Outcome 1)	Number of hospital bed days	Total number of hospital bed days residents accrued during the baseline and intervention exposure periods, accounting for RAC home occupancy levels.
Outcome 2	Emergency Department (ED) transfer rates	Resident transfers to emergency departments including mode of transfer, diagnosis code, triage category, length of stay (mins) and discharge outcome.
Outcome 3	Hospital admission rates	Residents admitted to hospital as an inpatient (exclusive of dialysis admissions) including diagnosis code (Australian Refined Diagnosis Related Group (AR-DRG)) and mode of arrival.
Outcome 4	Length of hospital stay and discharge outcome	Time (in days/hours) from admission to discharge for each episode of care including diagnosis code, time in intensive care unit and discharge outcomes.
Outcome 5	Family awareness and experience	Family or nominated advocate responses to a short questionnaire and/or interview to ascertain awareness of EDDIE+ and family perceptions and experiences of the program.
Outcome 6	Staff self-efficacy	Staff scores on the Job-related and Group-related Self-Efficacy measure [19]

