**Cost outcomes**		
Outcome 7	Cost of EDDIE+ implementation	The cost of implementing the EDDIE+ program will be measured by assigning profession specific wage rates, plus on-costs, to the duration of staff time associated with completing program activities (e.g. training, monitoring, facilitation). It will also include the costs of travel to sites, training materials and medical equipment.
Outcome 8	Cost of health service use	Health service costs to include ambulance transfers, ED presentations and hospital admissions.

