### Sample size calculation

A simulation-based statistical power calculation was performed for the primary outcome of total hospital bed days. The simulations used a stepped-wedge design of 12 sites of 100 residents per site with 1 site switched from baseline phase to intervention exposure phase each month as shown in Fig. 1. The study design was estimated to have a 91% power to detect a 41% reduction in total bed days from a baseline period total hospital bed days of 346 bed days per 100 residents per year [12]. The power calculation was based on a 5% statistical significance level.

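### Table 1 excludes dialysis from the admission rate (Outcome 3) but not from the primary bed-day total or length of stay; the distortion can be sizeable in one home but is small in the pooled estimate unless several homes are affected

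*Protocol article*

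**What the plan says.** All of the relevant definitions stand in Table 1 of the protocol article.

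- **Outcome 1 (primary):** "Total number of hospital bed days residents accrued during the baseline and intervention exposure periods, accounting for RAC home occupancy levels". Dialysis is not mentioned.
- **Outcome 3:** "Residents admitted to hospital as an inpatient (exclusive of dialysis admissions"). This is the only row that carries the exclusion.
- **Outcome 4:** "Time (in days/hours) from admission to discharge for each episode of care". Dialysis is not mentioned.
- **Outcome 8:** "Health service costs to include ambulance transfers, ED presentations and hospital admissions". Dialysis is not mentioned.

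The Analysis sections for the primary and secondary outcomes add no dialysis rule. Under Setting and participants, "Data on all residents at each enrolled RAC home will be collected as part of the study, with no exclusion criteria", so residents on dialysis contribute data. The Analysis section also commits to analysing Outcomes 1 to 6 in each home separately. The Sample size calculation claims "91% power to detect a 41% reduction in total bed days" from a baseline of "346 bed days per 100 residents per year".

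**The concern.** By excluding dialysis from Outcome 3, the authors show that they expect it to appear among inpatient admissions and that they do not want it in the admission rate. The same reasoning applies to the primary outcome. The program works by helping staff to recognise and manage early deterioration, and a scheduled dialysis attendance is not something it can prevent.

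Two things are at stake. First, days that the program cannot change dilute the bed-day ratio, and they add noise when a resident starts or stops dialysis, arrives, leaves or dies during the trial. Second, Outcomes 1, 3 and 4 no longer describe the same admissions, so a change in bed days cannot be split cleanly into fewer admissions and shorter stays. The Background presents the pilot's 41% reduction as just that combination. Many same-day episodes would also pull down the mean length of stay.

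**Working it through.** **Inputs from the article.** Baseline 346 bed days per 100 residents per year; target reduction 41%; power 91%; 5% level; 12 homes of 100 residents; one home switched per month.

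**Assumptions, not in the article.** One resident attends dialysis 1, 2 or 3 times a week; each attendance counts as one bed day; these days are not already in the 346.

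**The plan's own power figure.** The 91% came from simulation, and the article gives no home-month dispersion or between-home variance, so it can be neither reproduced nor refuted. As an approximation, take a Gamma model with log link, 12 homes, 13 months, a linear time term and a two-sided test: power = Φ(|ln 0.59| / SE − 1.96), where SE is proportional to the home-month coefficient of variation (CV). A power of 91% needs a CV of about 0.78 (no home effects) or 0.57 (home effects) if no introduction months are dropped, and about 0.65 or 0.45 if two are dropped per home. At a CV of 0.75, power runs from 51% to 93% across these set-ups. The stated figure is attainable but cannot be verified.

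**One home.** Targeted fall = 0.41 × 346 = 142 days a year, leaving 204. Added days = 52 × sessions per week. Apparent reduction = 141.86 / (346 + added days).

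| Sessions per week | Added days per year | Share of 346 | Share of targeted fall | Apparent reduction if the true fall is 41% |
|---|---|---|---|---|
| 1 | 52 | 15% | 37% | 141.86/398 = 36% |
| 2 | 104 | 30% | 73% | 141.86/450 = 32% |
| 3 | 156 | 45% | 110% | 141.86/502 = 28% |

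**All 12 homes, one such resident in total.** Baseline = 12 × 346 = 4,152; targeted fall = 0.41 × 4,152 = 1,702.

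- 1 a week: 52/4,152 = 1.3%; 1,702/4,204 = 40.5%.
- 2 a week: 104/4,152 = 2.5%; 1,702/4,256 = 40.0%.
- 3 a week: 156/4,152 = 3.8%; 1,702/4,308 = 39.5%.

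**Simulation of the pooled analysis.** Gamma regression, 500 replicates per scenario, CV set so that the approximation gives 91%, three sessions a week, fitted with and without home effects (ranges cover both).

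| Dialysis residents | Estimated ratio | Power |
|---|---|---|
| None | 0.588 | 0.92 |
| One home | 0.59–0.61 | 0.88–0.90 |
| Three homes | 0.61–0.63 | 0.82–0.90 |
| Six homes | 0.62–0.66 | 0.82–0.90 |
| Every home, throughout | 0.72 | 0.90 |
| Every home, starting or stopping mid-trial | 0.65–0.66 | 0.83–0.85 |

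A constant load mainly dilutes the ratio. A home intercept takes up the difference in level but does not undo the dilution. A start or stop within the trial is a change over time within a home, which an intercept cannot absorb.

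**Length of stay.** The article gives no mean stay. Assume 4 to 8 days for other admissions, which means 346/4 = 86.5 or 346/8 = 43.25 admissions a year in one home. At three sessions a week, the home's mean becomes 502/(86.5 + 156) = 2.1 or 502/(43.25 + 156) = 2.5 days. At one a week, it becomes 398/(86.5 + 52) = 2.9 or 398/(43.25 + 52) = 4.2 days.

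**The case against.** A reader might infer that one dialysis resident could overwhelm the primary outcome, or create or hide an effect in the trial. The documents do not support that. The primary coefficient is estimated across all 12 homes. Even at three sessions a week, one resident moves the crude reduction by only 1.5 points (41% to 39.5%). Within the affected home, those days are 156/502 = 31% of the combined total, so never the larger part. Clear attenuation in the simulation needs several affected homes, and nothing in the article indicates such a prevalence.

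Other points on that side:

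- **Counting rule.** The article does not define a bed day. If same-day attendances count as zero, the primary outcome is unaffected and only Outcome 4 is left in question. This stands, and is why the figures are conditional.
- **Baseline.** The 346 is itself called a total and may already contain dialysis days, in which case adding them again is wrong. This stands too; the article does not say.
- **Outcome 4.** It sits directly below Outcome 3, and the analysis text describes it as the stay of admitted patients, so it might be meant to inherit the exclusion. That is possible, but the row as printed covers every episode of care.
- **Outcome 8.** Counting all hospital costs is a legitimate choice, so its silence on dialysis is not an error. This stands in full.
- **The split of bed days.** No planned analysis depends on bed days equalling admissions times stay. True; the loss is in interpretation.
- **Condensed article.** The full protocol or analysis plan may hold the rule. It may, but the article prints the exclusion for a secondary outcome and omits it from the primary in the same table. It refers to Additional file 3 for residual checks and sensitivity analyses, not for outcome definitions.

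**Conclusion.** The mismatch is real: as printed, dialysis is out of Outcome 3 and in Outcomes 1 and 4. Its size is conditional on the three stated assumptions (attendance frequency, one bed day per session, and a 346 that excludes dialysis).

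On those terms it matters for the planned home-by-home analyses. There, one resident at three sessions a week adds more days than the whole targeted fall. For the pooled primary estimate it is a modest dilution and some loss of precision, becoming material only if several homes have dialysis residents. Mid-trial starts and stops then lower power, while constant loads attenuate the ratio most. The point is worth correcting because the remedy is cheap and the principle is already adopted for Outcome 3. It is not a threat to the trial's main conclusion on the evidence in the article.

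**What to change.** - Apply the Outcome 3 dialysis exclusion to Outcomes 1 and 4 in Table 1, using the AR-DRG and diagnosis codes that the trial already collects or obtains by linkage, and state how same-day attendances are counted.
- State whether the 346 baseline follows the same rule.
- Report dialysis days separately for the baseline and intervention exposure phases, so that the all-cause total can still be recovered.
- Leave Outcome 8 as total cost, optionally with a second version excluding dialysis.

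The cost is a wording change in Table 1 and one filter in the analysis code, with no new data. It should be settled before the analysis with true allocation; the scrambled-data report described under Analysis is a convenient occasion. The small downside is that the primary outcome becomes non-dialysis bed days. If the 346 includes dialysis, the baseline and the 41% target would need to be restated on the same footing.
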